# Effects of communication training with the MAAS-Global-D instrument on the antibiotic prescribing for respiratory infections in primary care: study protocol of a randomised controlled trial

**DOI:** 10.1186/s13063-016-1293-5

**Published:** 2016-04-02

**Keywords:** MAAS-Global-D, Communication skills, Physician-patient relationship, Antibiotic prescribing, Primary health care, Evidence-based medicine, Guidelines, Communicative competencies, Routine data, Respiratory tract infections

## Abstract

**Background:**

Primary care physicians account for the majority of antibiotic prescribing in ambulatory care in Germany. Respiratory diseases are, regardless of effectiveness, often treated with antibiotics. Research has found this use without indication to be caused largely by communication problems (e.g. expectations on the patient’s part or false assumptions about them by the physician). The present randomised controlled trial (RCT) study evaluates whether communication training for primary care physicians can reduce the antibiotic prescribing rate for respiratory tract infections.

**Methods/Design:**

The study consists of three groups: group A will receive communication training; group B will be given the same, plus additional, access to an evidence-based point-of-care tool; and group C will function as the control group. The primary endpoint is the difference between intervention and control groups regarding the antibiotic prescribing rate before and after the intervention assessed through routine data. The communication skills are captured with the help of the communication instrument MAAS-Global-D, as well as individual videos of physician-patient consultations recorded by the primary care physicians. These skills will also be regarded with respect to the antibiotic prescribing rate.

A process evaluation using qualitative as well as quantitative methods should provide information about barriers and enablers to implementing the communication training.

**Discussion:**

The trial contributes to an insight into the effectiveness of the different components to reduce antibiotic prescribing, which will also be supported by an extensive evaluation. Communication training could be an effective method of reducing antibiotic prescribing in primary care.

**Trial registration:**

DRKS00009566

**Date registration:**

5 November 2015.

## Background

Primary care physicians account for 67 % of antibiotic prescribing in ambulatory care in Germany [1]. In their family practices, respiratory diseases rank among the most frequent reasons for consulting [2]. In many of these cases antibiotic prescribing is not indicated and guidelines for bronchitis, sinusitis and pharyngitis recommend abstaining from antibiotic treatment for the vast majority of cases [3–7]. Rates of approximately 31 % antibiotic prescribing for respiratory diseases and approximately 60 % for pharyngitis/tonsillitis, however, leave room for substantial improvement [8]. Unnecessary use of antibiotics causes not only adverse drug reactions, but also contributes to antibiotic resistance and unnecessary health expenditure [9, 10]. It also reinforces patients’ incorrect assumptions regarding the effectiveness of antibiotics for respiratory diseases, which in turn influences their expectations when suffering from similar symptoms later on and triggers their belief in the need for antibiotics [11, 12]. Studies have found that inappropriate prescriptions of antibiotics cannot be attributed solely to a lack of knowledge in primary care physicians (PCPs). Equally important are falsely assumed patient expectations with regard to receiving medication [11, 13] in addition to PCPs feeling pressured by patients who ask for such medication [14] and wishing to maintain good relationships with patients or to avoid confrontations and the need to explain the differences between viruses and bacteria [11]. Physicians state that explaining takes up time and that explanations are often not understood by the patient, whereas prescribing antibiotics is a quicker and simpler course of action [11].

Studies have revealed the possibility of decreasing antibiotic prescribing in primary care by enhancing PCPs’ communication skills [15–17]. Communication training proved to be an effective intervention, sometimes paired with further elements, such as point-of-care testing, delayed prescribing or additional patient education material [12, 16–19]. The achieved effects were an absolute reduction of 10–12 % in the rate of antibiotic prescribing [15–17], corresponding to a relative reduction of 25-40 % [16, 18]. This reduction of antibiotic prescribing does not, or only to a very modest extent, impact negatively on patient satisfaction [12, 16, 17, 19]. Furthermore, a review on interventions to improve antibiotic prescribing concluded that multiple interventions, which contain more than one interventional module, are more likely to be effective than single intervention strategies [15]. Of the tested combinations of modules, educational meetings with educational material for the physician scored best [15]. Additionally, active clinician education strategies (e.g. interactive workshops) appear to be superior to passive ones (e.g. educational material only) [16].

Adequate communication skills are probably more important in primary care than in any other medical specialty. However, the German specialist medical training for PCPs lacks nationwide, structured training on communication skills [20]. This is in contrast to the situation in the Netherlands, for example, where an instrument to measure physicians’ communication and medical skills is incorporated in a structured curriculum on communication skills. The physicians record videos of physician-patient consultations which are then rated using the instrument produced to examine these skills. The instrument is now widely used in medical schools as well as in specialist training [21]. This instrument, named MAAS-Global-D, was recently translated and adapted for use in Germany [22]. Against this background, our study aims to investigate whether the rate of antibiotic prescribing can be reduced with the help of MAAS-Global-D-based communication training. We postulated the following research hypothesis:

In the intervention groups, the rate of antibiotic prescribing by PCPs for acute bronchitis, sinusitis and pharyngitis decreases following the communication training compared to the control group with no intervention.

Based on the MAAS-Global-D, we designed a multiple-component intervention, which, in brief, includes:Communication training for PCPs with interactive elements: the programme will be suitable for PCPs with professional experience. After the training sessions, the PCPs submit videos displaying their own communication with patients and receive feedback on it.Further information material for PCPs: they will be educated in the usage of Evidence-based Medicine – Guidelines (EbMG), a point-of-care tool, which will be made available online to one of the intervention groups during the whole study period and which aims to support and facilitate decision-making [23].

The groups compared will be:Group A:Intervention group A with communication trainingGroup B:Intervention group B, same training as group A plus access to EbMGGroup C:Control group C with no intervention 

By assessing and evaluating the communication training, it can be adapted and possibly also improved. Since the MAAS-Global-D instrument, as well as the associated manual, are published for free download, they will be available in order to establish nationwide training to decrease antibiotic prescribing in primary care and could be implemented in specialty training for PCPs later on.

### Objectives

#### Primary objective

To assess whether communication training for PCPs working in family practices in the federal state of Schleswig-Holstein (SH) in northern Germany leads to a reduction of antibiotic prescribing rates for acute bronchitis, sinusitis and pharyngitis compared to a control group (A + B versus C).

### Secondary objectives

To assess whether provision and training in the usage of EbMG leads to an additional reduction of antibiotic prescribing (A versus B)To assess whether PCPs who score higher on the MAAS-Global-D instrument (meaning they have better communication skills) as measured through videos of their consultations prescribe antibiotics less often than PCPs with a lower scoreTo evaluate the communication training as well as the use and the usefulness of EbMG by interviewing the PCPs in a process evaluation

## Methods/Design

### Trial design

The trial is designed as a randomised, controlled trial postulating superiority of the interventions over conventional care in family practices. The study consists of three arms and a primary endpoint of antibiotic prescribing rates of PCPs for acute bronchitis, sinusitis and pharyngitis over a 3-month period starting around 1 month after the communication training and education in the usage of EbMG. Randomisation of either of the two intervention groups or the control group will be performed at practice level with a 1:1:1 allocation. Therefore, random permuted blocks will be generated. Due to the data format, practices with more than one physician represent one case. The person assigning the participants to the groups will do so blinded. Further blinding does not fit the trial design.

### Study setting

The trial will be conducted in the population of PCPs in SH. In total, there are about 1900 PCPs in SH who are working in family practices, including rural as well as urban sites. In Germany, all resident PCPs belong to a subdivision of the Association of Statutory Health Insurance Physicians (KV). These subdivisions are responsible for the remuneration of physicians’ services when treating patients who are covered by statutory health insurance – approximately 87 % of all inhabitants [24]. Since 2011, all practices belonging to KV are obligated to do their accounting online, which requires a connection to the data centre of their KV. These routine data of the KV of Schleswig-Holstein (KVSH) will be the data basis for the present study concerning data about diagnoses. Information about prescriptions are obtained through a more complex process including pharmacies and the Central Research Institute of Ambulatory Health Care in Germany (ZI), but will also be provided by a federal subdivision of the KV together with data about diagnoses. Therefore, all data is referred to as ‘routine data’ in this article. For our objectives it is necessary to establish a connection between the PCPs and their data on diagnoses and antibiotic prescriptions. Each practice possesses an identification number, which can be used for this purpose. The study centre is located at the Institute of Family Medicine at the University Hospital of Luebeck (UKSH), SH. It will work in close collaboration with a KVSH data manager for the purpose of data analysis. Prior to analysis, official approval from the ‘Independent Regional Centre for Data Protection’ (Unabhaengiges Landeszentrum fuer Datenschutz) of the federal state of SH is sought.

### Interventions

The study incorporates a multiple-component intervention corresponding to the two interventional study arms (group A and B). Both intervention groups receive communication training with an interactive workshop character (4.5 hours of input), which is held at the Institute of Family Medicine. It is designed as a face-to-face delivery by members of the research team, including an expert on physician-patient communication.

Firstly, the speakers establish the relevance and success of physician-patient communication. The speakers then provide input concerning the associated evidence base. Furthermore, the participants learn the different communicative phases of a consultation, corresponding communication skills as well as general communication skills for the whole consultation (e.g. adequate provision of information, structuring and empathy, shared decision-making). These topics also function as an introduction to the MAAS-Global-D rating scale. The PCPs have the opportunity to evaluate a video with the recent learned criteria of the MAAS-Global-D, as well as to perform a consultation with a patient-actor themselves. The curriculum is derived from the aforementioned structured Dutch communication training, the MAAS-Global-D instrument, as well as from further evidence about successful physician-patient communication.

Group B receives an additional 1.5 hours of face-to-face input comprising education in the use of EbMG online. With online-access to this point-of-care tool, further information material on the prescribing of antibiotics for uncomplicated respiratory infections is provided for group B. The German version of the EbMG, which was originally developed in Finland, incorporates a regularly updated point-of-care tool with guidelines based on current best evidence, including videos, audio samples, pictures, links to evidence summaries and articles from the Cochrane library in addition to ready-to-print patient information [23]. It has received National Institute for Health Clinical Excellence (NICE) accreditation [25].

Another part of the intervention for both groups targets organisational matters: video recording in the PCPs’ practices, how to install the webcam and the informed consent forms for all patients. Each PCP receives a secure USB stick with a password that is used to transfer the videos to the study centre. To increase adherence, a monthly email will be sent to the participants reminding them of the videos and the book vouchers for each video.

The control group does not receive any intervention and provides ‘usual’ care to patients.

### Eligibility criteria

Written informed consent will thus be obtained from all participants: PCPs, their colleagues as well as patients to be filmed.

### PCPs

A PCP is defined as either a general practitioner or an internist working in primary care. Inclusion criteria are:PCPs who have been active members of KVSH for a minimum of 5 yearsprovide written, informed consentwork as a PCP in a practice, andin case they work with several PCPs in a group practice, all of them must give written, informed consent, since it is expected that a PCP in this working environment who receives the communication training will influence his colleagues

The exclusion criterion is:withdrawal of informed consent

### Patients

The patients involved in the video recording are recruited by the PCPs themselves in their own practices. Inclusion criteria are:written, informed consent before recordingminimum age of 18 yearsa first consultation about acute symptoms (though not necessarily about respiratory infections)^1^

The exclusion criterion is:insufficient knowledge of the German language

### Outcomes

#### Primary outcome measures

Evaluation of the antibiotic prescribing rate in both intervention groups compared to the control group between baseline (meaning the prescribing rate of the three periods April–June 2013, 2014, and 2015) and post-intervention (April–June 2016)

To determine the antibiotic prescribing rate for each PCP, all patients with the target-diagnoses of acute bronchitis, sinusitis and pharyngitis (classified by the *International Classification of Diseases*, *version 10* (ICD-10) codes: J01.-; J02.-; J20.- [26]) are identified in the routine data of KVSH and the proportion of these patients who receive antibiotic prescriptions is calculated. The three diagnoses and corresponding antibiotic prescriptions are condensed into one rate for each PCP (in %). This will be completed for two time periods (*t*_0_ = baseline, before intervention: mean of quarter II in the years 2013–2015; *t*_1_ = post-intervention: quarter II in the year 2016). For each PCP the change from *t*_0_ to *t*_1_ will be calculated (rate *t*_1_-rate *t*_0_). For each study group, the mean of the antibiotic prescribing rates of all PCPs in the group (at *t*_0_ and *t*_1_) will be calculated. For our primary endpoint the two intervention groups will be regarded as one group which is compared to group C.

#### Inclusion and exclusion criteria for data

To obtain the proportion of cases with the defined diagnoses and antibiotic prescribing for each PCP, the routine data are filtered for the following: inclusion of all cases with at least one visit to a PCP during time period *t*_0_ or *t*_1_, respectively, who were 18 years or older, had a diagnosis of acute bronchitis, sinusitis or pharyngitis. Exclusion if diagnosis of a further (bacterial) infection in the same quarter (ICD-10 codes A00.- till A37.-, A39.- till A79.-, J15.-, J17.- and J18.-). These cases need to be excluded because data about diagnoses are only available for each quarter and not on a daily basis. Furthermore, KVSH data about prescriptions cannot be linked directly to these diagnoses. If a patient is prescribed an antibiotic, it could either be for one of the defined diagnoses or another bacterial infection in the same quarter of the year. Hence all patients with the latter diagnoses are excluded. Furthermore, cases are excluded if multiple diagnoses of the defined diseases are made or the same diagnosis is made multiple times. Additionally, cases are excluded if they are diagnosed with a specific chronic disease (ICD-10 codes I50.-, J44.-, J45.-, C00-C75) or have a diagnosis related to pregnancy or childbirth (ICD-10 codes O). The presence of these diagnoses or the same diagnosis multiple times might qualify them as cases at higher risk or indicate a recurring disease where antibiotic prescribing is indicated. Eligible antibiotics are systemic antibiotics (40 different ATC codes, identified in [2]).

Using routine data is a fairly objective method in analysing prescribing behaviour compared to subjective methods such as interviewing patients retrospectively about their diagnosis and the antibiotics they received. Although this corresponds with high reliability, the validity might be compromised. ICD-10 codes and routine data might not represent the actual diagnoses and reasons for the consultation, but instead need to be completed for administrative reasons. Nevertheless, these limitations of routine data affect both intervention and control groups equally and, therefore, should not interfere with our results. Moreover, routine data is collected anyway and thus physicians are not burdened with additional documentation when participating in the study.

#### Secondary outcomes measures

Evaluation of antibiotic prescribing rate in intervention group A versus intervention group B between *t*_0_ and *t*_1_

The antibiotic prescribing rates calculated for the primary outcome will also be used for the analysis of the secondary outcomes, i.e. the mean of change in the antibiotic prescribing rate from *t*_0_ to *t*_1_. Study groups A and B will be compared to assess whether there is an additional effect in study group B due to using EbMG.Evaluation of antibiotic prescribing rates depending on PCPs’ communication skills

PCPs’ communication skills will be defined over their MAAS-Global-D score, which is computed by rating the PCPs’ videos with the MAAS-Global-D instrument. For this only the PCPs of the intervention groups are considered. For each PCP a mean score is calculated based on the six videos recorded during *t*_1_.

To evaluate the association between the MAAS-Global-D score and the antibiotic prescribing rate during *t*_1_, a linear regression will be calculated with each PCP’s antibiotic prescribing rate at *t*_1_ as dependent variable. Independent variables to be included in the model are the MAAS-Global-D score, the antibiotic prescribing rate at *t*_0_ and the difference between the two rates, the PCP’s field of specialisation, their kind of practice (single versus shared) and its location (urban versus rural) as well as the number of patients per quarter.To evaluate the communication training as well as the use and the usefulness of the EbMG by interviewing the PCPs

This process evaluation will be undertaken after *t*_1_ in terms of a qualitative, guided interview. As it is unlikely that all PCPs shall be willing to participate in the qualitative interview, additionally every participant is asked to fill in a semi-structured questionnaire with open and closed questions. The topics of both interviews will concern whether and in what way the communication training was helpful, which elements of it the PCPs used, further enablers and barriers to implementing our communication recommendations as well as additional feedback about the communication training.

A participant timeline along with the outcomes is provided in detail in the flow diagram in Fig. 1.

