## Discussion

The MAAS-Global-D instrument, which measures communicative and medical skills, has recently been translated into German [22] and will be tested in a randomised controlled trial in primary care in Germany for the first time. The trial design (three arms: multiple interventional elements and comparison with a control group) contributes to an insight into the effectiveness of the different components to reduce antibiotic prescribing, which will also be supported by extensive evaluation. Thereby, barriers and enablers to implement parts of or the whole of the communication training on a large scale will be worked out. The choice of active clinician education procedures and further educational material for the PCP, such as EbMG, would appear to be promising intervention strategies [15, 16].

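### The MAAS-Global-D score is defined as communication skill, although the protocol says the instrument also measures medical skills; an association with prescribing could not be credited to communication alone

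*Protocol article*

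**What the plan says.** All places are in the protocol article.

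- **Secondary outcomes measures** defines the predictor: "communication skills will be defined over their MAAS-Global-D score, which is computed by rating" the videos with the instrument. It then aggregates: "For each PCP a mean score is calculated based on the six videos recorded during" t1. This mean enters a linear regression with the physician's t1 antibiotic rate as dependent variable. The other covariates are the t0 rate, the difference between the two rates, specialisation, kind of practice, location and patients per quarter.
- **Secondary objectives** interprets the predictor: "PCPs who score higher on the MAAS-Global-D instrument (meaning they have better communication skills").
- **Background** describes the Dutch original as "an instrument to measure physicians’ communication and medical skills is incorporated in a structured curriculum on communication skills", and says that this instrument was translated and adapted for Germany.
- **Discussion** repeats it for the German version: "The MAAS-Global-D instrument, which measures communicative and medical skills".
- **Patients** (eligibility for filming) requires a first consultation for acute symptoms, "though not necessarily about respiratory infections".
- **Analysis, Secondary outcomes** limits the regression to groups A and B, to physicians with at least four videos, and gives it an exploratory purpose.

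**The concern.** Two sections describe an instrument with a communicative and a medical part. Two others treat its whole score as communication skill. This is a stated definition that does not fit the protocol's own description of the instrument, so it is more than a detail left for later.

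The label matters for this outcome. The Background says that guidelines recommend abstaining from antibiotics in most cases of the three target diagnoses. A low rate is therefore in part a sign of guideline-based medical practice. A score with a medical part can correlate with it even if communication plays no role. The Background also argues that excess prescribing is not only a matter of knowledge but equally of what passes between physician and patient. A regression meant to inform that argument should keep the two apart, and this predictor does not. A negative coefficient would invite the statement that better communicators prescribe less, when the data would support only a statement about physicians who score well on communicative and medical skills together.

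**Working it through.** **No figure to reproduce.** The document states no number for this regression: no item list, no weights, no expected association. The one figure borrowed is the 28 physicians per arm from the Sample size section, which gives 2 × 28 = 56 in A and B. It reproduces: a two-sided Satterthwaite t test with difference 12, SDs 15.6 and 19.2 and A+B to C at 2:1 has 80.1 % power with 28 controls and 78.6 % with 27.

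**Step 1: the model as printed.** Since t1 rate = t0 rate + (t1 rate − t0 rate), the t0 rate and the difference reproduce the dependent variable exactly. A test fit gave coefficients 1 and 1 for these two, 0 for the score, and zero residual. Whatever the score contains, its coefficient is zero. This is a separate fault. What follows assumes that the difference has been removed.

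**Step 2: what a mixed score can produce.** Assumptions, none from the document:
- score = (1 − w) × communication + w × medical, the parts being uncorrelated with equal variance;
- communication has no association with prescribing;
- the medical part correlates −r with the t1 rate given the t0 rate.

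The correlation of the score with the t1 rate given t0 is then −r × w / √(w² + (1 − w)²). With r = 0.4:
- w = 0.2: −0.4 × 0.2 / 0.825 = −0.10
- w = 0.3: −0.4 × 0.3 / 0.762 = −0.16
- w = 0.5: −0.4 × 0.5 / 0.707 = −0.28

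With 56 physicians and the t0 rate as the only other covariate (53 residual degrees of freedom), significance at two-sided 5 % needs an absolute correlation of 2.006 / √(2.006² + 53) = 0.27. Of these three, only w = 0.5 gives an expected value beyond it.

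**Step 3: chance of a significant score coefficient with no communication effect.** Simulation of the same model, 4,000 runs per cell:

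| Medical share w | r = 0.3 | r = 0.5 | r = 0.8 |
|---|---|---|---|
| 0 | 5 % | 5 % | 5 % |
| 0.1 | 5 % | 7 % | 10 % |
| 0.2 | 7 % | 15 % | 29 % |
| 0.35 | 18 % | 42 % | 83 % |
| 0.5 | 35 % | 75 % | over 99 % |

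The row w = 0 is a score built from communication items only; it keeps the nominal 5 %.

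**The case against.** **The medical part is not shown to grade the antibiotic decision.** A reader might infer that the predictor partly contains the outcome, because a rating of medical skill could judge the treatment given. The document does not support this. It lists no items and does not say that any item rates treatment or prescribing. The filmed consultations need not be respiratory. The outcome is the proportion treated among all eligible cases in the quarter, from routine data, while the score rests on six videos that the physician chooses. Direct overlap would need both respiratory videos and items that rate management. This part of the objection stands, and the overlap reading should not be used. The indirect route through general medical quality remains.

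**The t0 rate is in the model.** A stable tendency to follow guidelines would already show in three years of baseline prescribing, and adjustment would absorb part of it. This is right as far as it goes. The simulation defines r given t0, so it concerns only what the adjustment leaves; small values of r may be the realistic ones.

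**Which items form the score belongs in a manual or analysis plan.** That would hold if the article were silent. It defines the whole score as communication skill and elsewhere says that the instrument measures more.

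**The analysis is minor.** It is secondary and exploratory and covers the intervention arms only. The case for the training rests on the randomised comparison of A+B with C. This stands and limits the weight of the point.

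**Conclusion.** The point holds as a mismatch between the named construct and the score that is to represent it. As defined, an association between the MAAS-Global-D score and antibiotic prescribing at t1 cannot be credited to communication alone, since general medical quality may contribute.

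Its size cannot be fixed from the document. The range from 5 % to over 99 % in the table only shows that the problem can be negligible or dominant; it is no estimate. It rests on assumed weights, on uncorrelated parts and on an assumed link between medical skill and prescribing.

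The reach is narrow: one exploratory regression in groups A and B, and only after the t1 − t0 difference has been taken out of the covariates. The primary comparison is unaffected. The point is worth correcting mainly because correction is cheap.

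**What to change.** 1. In Secondary outcomes measures, define the predictor as the mean of the communication items of the MAAS-Global-D, averaged over the videos. The Interventions section already speaks of phase-specific and general communication skills as the introduction to the rating scale.
2. Report the medical-skill items as a separate score and enter it as a covariate in a supportive model.
3. If the total score is kept, or if the items cannot be separated, describe it as communicative and medical skill in Secondary objectives and Secondary outcomes measures, and word the conclusion accordingly.
4. A sensitivity analysis without videos on the three target diagnoses is optional, and possible only where the reason for consultation is known. It should not be a main analysis, because dropping videos could take physicians below the four-video minimum.

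**Cost.** A change of wording, with no new ratings provided that item scores are kept. Fewer items lower the reliability somewhat. The article gives Cronbach's α of 0.78 to 0.86 for the English version. If a fraction k of comparable items remains, the Spearman-Brown formula gives kα / (1 + (k − 1)α). With k = 0.8 (assumed) this is 0.624 / 0.844 = 0.74 to 0.688 / 0.828 = 0.83. The loss grows if the medical part is larger.
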